## 4. Conclusions

In summary, our protocol will evaluate the therapeutic effects of intradialytic exercise programs for HD patients given at different frequencies. With our results, we should be able to determine whether lowering the frequency of intradialytic exercise brings similar therapeutic effects in the Asian population of Taiwan.

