Despite the benefits aforementioned, the intradialytic exercise program is not commonly incorporated into regular HD care worldwide. After all, the formal recommendation from the ACSM is to perform exercise training for a minimum of two hours after, but not during, HD [10]. In Taiwan, no HD unit incorporates an exercise program as part of regular care. Very few studies have evaluated the effects of structured intradialytic exercise programs on the level of physical activity and HRQoL of HD patients [13,14,15]. According to the ACSM’s guideline for an exercise prescription [10], the frequency of aerobic exercise for HD patients is 3 to 5 days per week. Whether a low frequency of exercise (such as two days per week) produces similar therapeutic effects is unclear. The objective of this randomized control trial is, therefore, to compare the efficacy of different frequencies of structured intradialytic exercise programs on Asian HD patients in Taiwan.

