### 2.5. Statistical Analysis and Power Estimates

Statistical analyses will be performed using SPSS, version 22.0 (SPSS Inc., Chicago, IL, USA). The Shapiro–Wilk test of normality will be used to evaluate the distribution of each outcome variable. If data are normally distributed, paired t*tests and analysis of variance (ANOVA) will be used. If data are not normally distributed, the Wilcoxon signed-rank test and Kruskal–Wallis test will be used. The preintervention outcome measures will be compared using ANOVA or Kruskal–Wallis test. Paired t-tests or Wilcoxon signed-rank test will be applied to compare differences between pre- and post-tests. After the exercise intervention, intergroup comparisons regarding improvements of outcome measures will be determined using ANOVA or Kruskal–Wallis test.

The G*Power (Germany, version 3.1.9) software will be used for sample size estimation [22]. Based on repeated measures ANOVA, a statistical power of 0.8, a significant level of 0.05, the effect size is 0.35, refs. [23,24,25], and a minimum of 84 participants are required for our study. We noted the likelihood of a high drop-out rate for intradialytic exercise [26].

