Most intradialytic exercises in the literature, including the best-known CYCLE-HD study, were conducted for 30 min and given three times a week [11,13,14,15,16]. There is only one study that used the exercise frequency of two times a week, and the training mode involved resistance training and stretching, but not aerobic training [44]. Some other studies also adopted the exercise frequency of two to three times a week, such as those of Vilstreren et al., Chigira et al., and Bae et al. [45,46,47]. To our knowledge, no study has yet directly compared intradialytic exercise groups specifically between three times and two times a week. Since cycle ergometer devices and healthcare givers monitoring intradialytic exercise may be limited in some hospitals in different countries, whether the frequency of intradialytic exercise could be reduced is a crucial and practical issue that needs to be clarified. Hence, we have designed this comparative study in order to clarify this issue and try to fill the knowledge gap in the field of intradialytic exercise.

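### The Conclusions promise to determine whether twice-weekly exercise is similar to thrice-weekly, but the stated three-group difference test cannot answer that question

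*Protocol article*

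**What the plan says.** Three places in the protocol article set up the frequency question.

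- Section 1 (Introduction): "Whether a low frequency of exercise (such as two days per week) produces similar therapeutic effects is unclear". The objective follows from this as a comparison of the efficacy of different frequencies.
- Section 3 (Discussion): "no study has yet directly compared intradialytic exercise groups specifically between three times and two times a week", and, because equipment and staff may be scarce, "whether the frequency of intradialytic exercise could be reduced is a crucial and practical issue that needs to be clarified".
- Section 4 (Conclusions): "we should be able to determine whether lowering the frequency of intradialytic exercise brings similar therapeutic effects in the Asian population of Taiwan".

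Section 2.5 then states the analysis. Within each arm, "Paired t-tests or Wilcoxon signed-rank test will be applied to compare differences between pre- and post-tests". Between arms, "intergroup comparisons regarding improvements of outcome measures will be determined using ANOVA or Kruskal–Wallis test". The arms, from section 2.2.2, are three sessions a week, two sessions a week, and usual care. The sample size is also built on a difference test: "Based on repeated measures ANOVA, a statistical power of 0.8, a significant level of 0.05, the effect size is 0.35", giving a minimum of 84 participants.

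**The concern.** The question concerns one pair of arms and asks whether they are alike. The stated test concerns all three arms and asks whether any of them differ. Neither outcome of that test answers the question.

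- **Significant.** The cause may be that both exercise arms beat usual care by the same amount. This says nothing about frequency.
- **Not significant.** The data did not establish a difference. They may still be compatible with a large loss from dropping a session.

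The within-arm pre/post tests do not help, because improvement in each exercise arm is not a comparison of the two. The Discussion ties the answer to whether units can run fewer sessions, so an unsupported finding of similarity would bear on practice.

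**Working it through.** **Inputs.** From section 2.5: effect size 0.35, alpha 0.05, power 0.80, minimum N = 84. From section 2.2.2: three arms. Assumptions, because the article does not state them: 0.35 is Cohen's f; allocation is 1:1:1, so 28 per arm; differences are in SD units of the analysed change score; dropout is either 0% or about 20% (22 per arm). The article calls dropout likely to be high but gives no rate.

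**1. Reproduce 84.** For a one-way three-group ANOVA the noncentrality is λ = f²N.
- N = 84: λ = 0.1225 × 84 = 10.29, df 2 and 81, power 0.812.
- N = 81 (27 per arm): λ = 9.92, power 0.796, just short.

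So 84 is the smallest total with equal arms that reaches 0.80 in an omnibus three-group test. The article names a repeated measures ANOVA as the basis. That too is a test of difference, so the point does not depend on which was run.

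**2. What f = 0.35 means for the pair of interest.** f is the SD of the three true means divided by the within-group SD. Different patterns of means give the same f.

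| True pattern (all f = 0.35) | Gap, three vs two sessions | Omnibus power, N = 84 | Pairwise power, 28 per arm |
|---|---|---|---|
| Both exercise arms equal, above usual care | 0 | 81% | none to detect |
| Equally spaced: 0, 0.43, 0.86 SD | 0.43 SD | 81% | 35% |
| Twice weekly equal to usual care | 0.74 SD | 81% | 78% |

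The gaps are 0.35 × √6 / 2 = 0.43 SD for equal spacing, and 0.35 × 3/√2 = 0.74 SD when two arms coincide. Pairwise power uses the noncentral t with df = 54, noncentrality d√(28/2), two-sided 0.05. The omnibus test behaves identically in all three rows, although the answer to the frequency question is different in each.

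**3. Precision of the pair.** The half-width of the 95% interval is t(0.975, 2n − 2) × √(2/n).
- n = 28: 2.005 × 0.267 = 0.54 SD.
- n = 22: 2.018 × 0.302 = 0.61 SD.

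**4. Could similarity be shown at this size?** The article gives no margin, so a range is assumed (one-sided 0.025, true difference zero).

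| Assumed margin | Non-inferiority power, 28 per arm | Per arm for 80% power |
|---|---|---|
| 0.3 SD | about 20% | 175 |
| 0.5 SD | about 45% | 63 |
| 0.75 SD | about 79% | 28 |

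The second column uses the noncentral t and the third a normal approximation. This counts only the side of loss. A two-sided requirement is harder: a 95% interval with half-width 0.54 SD cannot fit inside ±0.5 SD.

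**The case against.** The best defence is that the formal objective is to compare efficacy, and the abstract says that the difference between the two frequencies has never been determined. Difference tests suit both in kind, and no equivalence or non-inferiority hypothesis is stated. That is fair, but it does not dispose of the Conclusions, which promise to determine similarity, or of the Introduction, which frames the gap in the same terms. Even read as a pure difference question, the three-group test does not isolate the pair.

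Second, follow-up contrasts, intervals or a margin may sit in a full protocol or analysis plan that is not shown. This stands, so their absence is not counted here. A reader might infer that the ANOVA is the only between-arm test that will be run. The article speaks of intergroup comparisons in the plural and neither names nor rules out pairwise ones, so it does not support that. What remains is a mismatch in the printed text, and no later document changes the ±0.54 SD precision that 84 participants give.

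Third, the pairwise power depends on assumptions. This stands as well: 35% needs equal spacing, and another pattern with the same f gives 78%. In addition, 84 is a stated minimum, so 28 per arm is a floor on planned enrolment.

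**Conclusion.** The point holds. The Conclusions promise more than the stated analysis and sample size can deliver: a three-group difference test, sized at 84 for a three-group difference, cannot determine whether two sessions a week are similar to three. That logic needs no assumption about effect sizes.

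The figures are conditional on 1:1:1 allocation and on 0.35 being Cohen's f. The interval for the pair is then about ±0.54 SD with full follow-up and ±0.61 SD with about 20% dropout. Pairwise power is 35% or 78% depending on a pattern of means that the article does not give.

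Two stronger readings are not supported. One is that the trial will take a non-significant p-value as similarity: the article says only that it should be able to determine *whether* effects are similar, which leaves either answer open. The other is that the comparison has 35% power without qualification.

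**What to change.** **Section 2.5.**
- Name the three-minus-two difference in change, with its 95% confidence interval, as the comparison that answers the frequency question. Keep it separate from exercise versus usual care.
- Attach it to one prespecified SF-36 summary score at one prespecified time point. Section 2.4.1 lists eight subdomains and two component scales without singling one out, so the sponsor must choose (for example, the physical component scale).
- State that a non-significant test will not be read as similarity, and that similarity will be claimed only if the interval lies within a margin fixed before data are seen.

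**Section 4.** Replace the promise to determine similarity with a promise to estimate the three-minus-two difference, giving the expected precision (about ±0.54 to ±0.61 SD under the assumptions above).

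**Cost.** Wording in two sections, one added contrast, and the choice of a score, a time point and a margin. Recruitment, randomisation and data collection are unchanged. The real price is candour: at this size similarity probably cannot be shown, with non-inferiority power of about 45% even at an assumed margin of 0.5 SD. Answering that question with 80% power at that margin would take 63 per arm, before dropout.

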## Figures and Tables

**Figure 1 healthcare-10-01103-f001:**
[figure not shown]
Study timeline.

## Data Availability

Not applicable.
